## Abstract

**Background:**

Multiple studies have shown the efficacy of Systemic Psychotherapy (ST) approaches as a promising path to address various mental health disorders and alleviate psychological distress. One promising path that requires further investigation is online self-help interventions and paraprofessional training. Our study aims to evaluate the implementation of delivering ST-informed online self-help interventions (OSI) and paraprofessional training in a naturalistic setting via the 7 Cups platform.

**Methods:**

Our exploratory, randomised, controlled, pre-post-follow-up study is recruiting two samples of participants: (i) for the ST-informed online self-help/growth path intervention amongst members on the 7 Cups platform, (ii) for the ST-informed online paraprofessional/listener training intervention amongst members who have registered as ‘listener’ status. The sample size target is *N* = 200 participants, randomly assigning and comparing 50 OSI member participants to 50 waitlist member participants and 50 paraprofessional/listener training listeners to 50 waitlist listener participants. Our sample size justification, based on previous feasibility studies and guidelines, suggests that a sample size of 50 per group, accounting for a 25% attrition rate, is sufficient to assess feasibility in online family, e-health, and mental health trials, while maintaining narrow margins of error for confidence intervals and primary outcome parameters. The primary outcome is non-specific psychological distress (Kessler Psychological Distress Scale; K6); secondary outcomes include perceived stress, anxiety and depressive symptoms, and momentary mood. To estimate intervention effects, we intend to conduct generalised linear mixed models of primary, and secondary parameters, adjusted for potential covariates (e.g., gender, age categories, socioeconomic status) as fixed effects.

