## Methods and design

### Overview of research project and study design

The main components of our study are:

i)An exploratory, randomised, controlled trial following the definition of the National Institute for Health Research UK (NIHR UK) in a natural setting, pre-post-follow-up design with two parallel comparisons:
the 2 arm ST-informed OSI (growth path) intervention compared with a waitlist comparator condition among 7 Cups members, and,the 2-arm ST-informed paraprofessional provider/listener training compared with a waitlist comparator condition among 7 Cups listeners.

Each comparison uses a 1:1 allocation ratio. Figure 1 displays participant flow in each sub-study, including randomization to intervention vs. waitlist and subsequent follow-up assessments. Although this is not a fully powered randomized controlled trial (RCT), randomization will be used to test the procedure and to gather exploratory efficacy data.

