### Outcomes

Our outcomes are divided into primary and secondary outcomes. We provide a full list of assessment instruments in Table 1 which also includes the list of primary and secondary endpoints. The primary outcome of our study is the Kessler Psychological Distress Scale 6 (K6), which is a standardised self-reported outcome assessment tool used to measure global non-specific psychological distress with questions relating to depressive and anxiety symptoms. We selected the K6 for its brevity and validation in community-based samples ranging from subclinical to clinical distress [41, 42]. Although floor effects are a possibility in individuals without any significant distress, our preliminary assessments and data from 7 Cups suggest that a noteworthy proportion of participants have mild to moderate distress, making the K6 a pragmatic primary outcome measure. The primary endpoint of the study is the scores of the K6 assessment instrument, which consists of 6 items asking participants to rate their emotional states on a 5-point Likert scale ranging from ‘All the time’ to ‘None of the time’. The K6 is a widely used and accepted assessment instrument for measuring mental health-related intervention outcomes with confirmed reliability and validity. The K6 has good psychometric properties in the general population and is considered reliable with excellent internal consistency reliability of 0.89 [41, 42].

**Table 1 Tab1:** Measures and timepoints

Measure	Time point			References
	Pre	Post	Follow-Up (Post + 2 weeks)	
K6	x	x	x	Cornelius et al., 2013
PSS-4	x	x	x	Warttig et al., 2013
PHQ-4	x	x	x	Kroenke et al., 2003
UMUX-LITE		x*		Finstrad, 2010
MDMQ (4-item)	x	x	x	Steyer et al., 1997
Qualitative questions		x		
Sociodemo- graphic and other general information	x			

Abbreviations: K6, Kessler Psychological Distress Scale 6; PSS-4, Perceived Stress Scale-4; PHQ, Patient Health Questionnaire; UMUX-LITE, Usability Metric for User Experience; MDMQ, Multidimensional Mood State Questionnaire

*is not completed by subjects in waitlist condition

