### Sample size

According to Bilingham et al., (2013) [49] sample size justification is very important, but power calculations may not be appropriate for feasibility studies. Following the recommendations of Gallinat et al., (2018) [50] and Leon, Davis and Kraemer (2011) [51], a sample size of 50 per group, considering potential attrition of 25%, is sufficient for feasibility studies. This sample size allows us to assess feasibility in online family, e-health, and mental health trials for recruitment capabilities, data collection and randomization procedures, participant flow, adherence, and acceptability [49–53] and is still sufficiently large to estimate rough variance for continuous outcomes and trends in expected direction and implementation of outcome measures [49]. We acknowledge that an exploratory study with a small sample size will need to be interpreted cautiously [51]. We thus aim to recruit *N* = 200 participants: 100 *members* (50 in the ST-informed online self-help condition and 50 in the waitlist) and 100 *listeners* (50 in the ST-informed paraprofessional training condition and 50 in the waitlist). Therefore, our targeted sample size of 200 participants should be viewed as supporting an *exploratory* aim. Future trials with a larger sample size will allow a more precise estimation of effect sizes.

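### The abstract claims narrow margins of error for the primary outcome, but no margin is derived and the Sample size section claims only rough estimates

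*Protocol article*

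**What the plan says.** The Abstract (Methods) bases 50 per group on earlier feasibility studies and guidelines. It judges that number enough to assess feasibility after 25% attrition, and adds "while maintaining narrow margins of error for confidence intervals and primary outcome parameters". The next sentence names the K6 as the primary outcome.

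The Sample size section gives the full rationale. It states that "power calculations may not be appropriate for feasibility studies" and that "a sample size of 50 per group, considering potential attrition of 25%, is sufficient for feasibility studies". It lists the feasibility aims (recruitment, data collection, randomisation, flow, adherence, acceptability) and then describes the number as "sufficiently large to estimate rough variance for continuous outcomes and trends in expected direction". It asks for cautious interpretation and expects larger future trials to estimate effects more precisely. The recruitment target is 100 members ("50 in the ST-informed online self-help condition and 50 in the waitlist") and 100 listeners split in the same way. The design overview adds "Each comparison uses a 1:1 allocation ratio" and says that the trial is not fully powered.

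Neither place gives a margin of error, a confidence level, a K6 standard deviation or an interval width.

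**The concern.** The abstract reports a property of the sample size justification that the justification does not contain. The Sample size section promises a rough variance and a direction, while the abstract promises tight intervals, including for the primary outcome. Both cannot describe the same design.

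The abstract is the part most often read. The second research question asks whether the self-help intervention is efficacious against waitlist, and the Discussion states a hypothesis of greater reduction in distress. Someone who relies on the abstract could take a small K6 difference as good evidence of no effect, or a sizeable one as well estimated.

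**Working it through.** **What can be reproduced.** The protocol gives no numerical margin, so there is none to reproduce. The total does check: 4 × 50 = 200.

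**Inputs from the protocol article.** 50 recruited per arm, 25% attrition and 1:1 allocation within each of two separate comparisons (Sample size; design overview). K6 score is the primary outcome (Outcomes).

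**Assumptions of this review.** Two-sided 95% intervals; results in SD units because no K6 SD is given; a baseline to follow-up correlation r of 0.5 to 0.7 for the adjusted case.

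**Completers.** 50 × (1 − 0.25) = 37.5 per arm, that is 37 to 38.

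**K6 between-group difference.** Half-width = t(0.975, 2n − 2) × √(2/n), in SD units.

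| Case | Calculation | Half-width |
|---|---|---|
| 37.5 per arm, unadjusted | 1.993 × √(2/37.5) | 0.460 SD |
| 50 per arm, no attrition, unadjusted | 1.984 × √(2/50) | 0.397 SD |
| 37.5 per arm, baseline-adjusted, r = 0.5 | 1.96 × √(2/37.5) × √(1 − 0.25) | 0.392 SD |
| 37.5 per arm, baseline-adjusted, r = 0.7 | 1.96 × √(2/37.5) × √(1 − 0.49) | 0.323 SD |

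The adjusted rows use the normal quantile; with it, the unadjusted value at 37.5 is 0.453 SD. For an assumed K6 SD of 4 to 6 points and 38 per arm, 1.96 × SD × √(2/38) gives about 1.8 to 2.7 points.

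**What this width means.** At ±0.46 SD, an observed difference of 0.10 SD has an interval from −0.36 to 0.56 SD, and one of 0.40 SD has an interval from −0.06 to 0.86 SD. At the most favourable value shown, ±0.32 SD, an observed 0.20 SD runs from −0.12 to 0.52 SD. In each case both no effect and an effect of 0.5 SD remain possible. For scale, a half-width of 0.2 SD would need 2 × (1.96/0.2)² ≈ 192 analysed per arm.

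**Feasibility proportions.** Half-width = 1.96 × √(p(1 − p)/n).

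| Denominator | p = 0.75 | p = 0.50 |
|---|---|---|
| One arm, all 50 randomised | 12.0 points | 13.9 points |
| One arm, about 38 completers | 13.8 points | 15.9 points |
| Both arms of one sub-study, 100 randomised | 8.5 points | 9.8 points |

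**Does the weaker wording fit?** The 95% limits for an SD are the estimate times √((n − 1)/χ²). With n = 38 the factors are 0.82 and 1.29; with n = 50 they are 0.84 and 1.25. That is a rough variance, as the Sample size section says.

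**The case against.** **Narrow has no threshold in the protocol, and no figure is miscalculated.** This stands. Calling 0.46 SD wide is partly a judgement. The conflict between the Abstract and the Sample size section, however, needs no threshold.

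**The planned analysis is not an unadjusted comparison of completers.** It is a covariate-adjusted generalised linear mixed model, and K6 is measured at three time points. This also stands: 0.46 SD should not be read as the precision of the planned analysis. The covariates named as examples are gender, age category and socioeconomic status. If baseline K6 is used as well, the half-width falls to about 0.32 to 0.39 SD under the assumed correlations, which is still a large part of 0.5 SD.

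**The phrase about primary outcome parameters may not mean the group difference.** It could mean a single-arm mean, for which the half-width at 37.5 is t(0.975, 36.5)/√37.5 = 0.33 SD. That reading does not make the claim supported either, since no margin is given for any parameter.

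**The authors already limit their claims.** They do. The Background disclaims conclusive claims, the design overview and Discussion say the trial is not fully powered, and the Sample size section asks for caution. This reduces the harm, but it also shows that the abstract's clause is out of line with the rest of the article.

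**Conclusion.** The abstract's precision clause is unsupported and conflicts with the article's own Sample size section. On two-sided 95% intervals the K6 difference would be known to about ±0.46 SD unadjusted with 37 to 38 completers per arm, ±0.40 SD with no attrition, and about ±0.32 to 0.39 SD with baseline adjustment at an assumed r of 0.5 to 0.7.

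Three stronger readings are tempting and do not hold:

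- *Precision is the basis for the sample size.* It is a trailing clause; the stated basis is feasibility, earlier studies and guidelines.
- *The sample is too small.* For a feasibility aim, 50 per group is not shown to be wrong, and power is not the criterion that the protocol chose.
- *The lack of a definitive efficacy answer is a hidden flaw.* The authors say so themselves.

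**What to change.** Delete the clause on margins of error from the Abstract and describe precision there as the Sample size section does.

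Alternatively, replace it with expected half-widths, each with its denominator and stated as 95% intervals:

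- K6 between-group difference: about ±0.46 SD, unadjusted, with 37 to 38 completers per arm.
- Single-arm feasibility proportions between 75% and 50%: about ±12 to 14 points with all 50 randomised, or about ±14 to 16 points among about 38 completers.

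The denominators should not be mixed: the 12 to 14 point range belongs to 50, not to the completers used for the K6 figure. If the second option is taken, the same figures belong in the Sample size section.

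No change to the sample size or the analysis is needed. The cost is a change of wording and a less favourable stated precision.

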**Discussion:**

Despite the great need for mental health interventions, there is limited research available showing the efficacy of digitally delivered ST-informed interventions. This exploratory, randomized, controlled trial will yield robust insights into the feasibility, challenges, and user experience of novel, digital interventions on a widely accessible online platform (7 Cups).

**Trial registration:**

ClinicalTrials.gov (NCT06017414, updated 21.11.2023). Registered 29 August 2023, https://clinicaltrials.gov/study/NCT06017414.

**Supplementary Information:**

The online version contains supplementary material available at 10.1186/s13690-025-01597-1.

**Table Taba:** 

**Text box 1. Contributions to the literature**	
• This study protocol addresses a gap in the public health literature by evaluating a digital, systemic therapy-based self-help and paraprofessional program.	
• It explores how training non-professionals alongside guided self-help can expand and strengthen mental health support globally, reaching people who lack access to traditional services.	
• The findings may help guide future research and practice on integrating systemic therapy principles into digital mental health strategies to reduce psychological distress on a large scale.	

## Background

The efficacy of family and parenting interventions is well-established for treating various mental health disorders [1–3]. Multiple studies have shown the efficacy of these interventions delivered digitally [4, 5]. However, definitions of family and parenting therapies can often be broad and defined more by the setting than the content of the intervention. Systemic Psychotherapy (ST) contains multiple elements of family and parenting interventions and provides a more unified definition, characterised by the content of the intervention rather than the setting. In recent years, ST has received an increasing amount of attention and acknowledgement, such as the 2017 report by the *Institut für Qualität und Wirtschaftlichkeit im Gesundheitswesen (IQWiG)*, a comprehensive systematic review outlining the efficacy and effectiveness of ST in treating the most common mental health disorders [6], the official declaration and integration of ST into the German public healthcare system in 2018 by the *Gemeinsame Bundesausschuss (G-BA)*, as well as various other comprehensive systematic reviews and meta-analyse [7, 8]. While individual definitions of ST differ, there are certain characteristic core elements and principles that allow for a largely agreed-upon and usable definition based on the following principles and techniques: an emphasis on relational and social systems, neutrality or multipartiality, focusing on individuals’ and systems’ resources, recognizing interpersonal patterns that contribute to psychological distress, and techniques such as joining, contracting, linework, witnessing and sculpture work [9–12]. Various systematic reviews (e.g. Carr [2], IQWiG, [6]; Riedinger et al., [7] highlight these components as characteristic of ST and fundamental in distinguishing it from individually oriented treatments. In this study, we integrate these principles and techniques in both the self-help and paraprofessional training programs, thus referring to them as ST-informed [6, 12]. For research and practice, ST can be characterised as “intervention into complex human systems (both, psychological and interpersonal) with the aim of reducing or eliminating suffering” [13] (translated by MB). ST can further be defined as a conceptual framework for mental health interventions that incorporate interpersonal relations, social interactions, perspectives, constructions of situations and problems, and appreciating and utilising attempted solutions as an integral part of the intervention [7, 9, 14]. Although systemic therapy is often delivered to couples, families, or other relational systems, it is also the case that individual-focused ST adaptations can be used to leverage systemic principles in an individual context (e.g., encouraging an individual to explore relational patterns and multi-perspective taking) [2, 6, 15]. Our digital modules similarly focus on these relational perspectives and interactions, even though each participant completes the program individually. Although research has supported the efficacy of ST interventions, further research is required. It is of crucial importance to critically evaluate ST interventions to avoid potential *culs-de-sac*, as well as to identify the most promising paths for efficacious interventions and ‘’conditions under which systemic therapy works best’’ [7], (p. 881).

Similar to digitally delivered interventions of family therapy interventions [16, 17], digitally delivered ST in the form of online self-help interventions (OSIs) may be one such promising path. This approach is particularly promising as digital delivery continues to advance and may help to overcome some of the common impediments to the worldwide delivery of psychotherapy such as limited access [18, 19], cost, and stigma [20]. While ST has been validated primarily in clinical populations, data suggest its approach may also benefit non-clinical users who experience stress or mild psychological distress [2, 5, 21–23]. Because 7 Cups members and listeners do not necessarily have formal diagnoses, this study seeks to determine if an ST-informed approach can be feasibly applied and beneficial to a broader population, including subclinical or undiagnosed distress. OSIs can be broadly divided into guided and unguided modes of self-help, with the former showing better efficacy than the latter [24]. This distinction notwithstanding, unguided OSIs are effective in the treatment of anxiety [25], depression [26], the prevention of suicides [27], and numerous other mental health disorders and conditions [28]. From a public health perspective, OSIs are particularly interesting as they promise to address several obstacles to conventional mental health care provision and harness patients’ capacities for self-help [29]. Additionally, their scalability might facilitate the provision of services to target groups that could otherwise not be reached [30]. While there still appears to be some level of discrepancy in terms of perceived acceptability in patients and practitioners (the latter rating acceptability lower than the former) [28], OSIs are particularly effective within so-called “blended care” approaches, integrating OSIs with face-to-face treatment [31]. Another way in which OSIs might prove a useful addition to existing modes of treatment is within a so-called “stepped care” approach where OSIs function as a first “step up” following prevention and diagnostics and preceding other forms of treatment such as face-to-face psychotherapy [32]. Platforms like “7 Cups” (https://www.7cups.com) offer self-help, text-based paraprofessional support, and signposting to professional services, which aligns with some recommendations and prior research in digital mental health research on the 7 Cups platform [1]. Further, systematic reviews indicate that platforms combining self-guided digital content with human support can be especially promising (see Sin et al. [33] for a general review of digital interventions). Although systemic therapy is commonly delivered to couples, families, or other relational systems, it is also the case that individual-focused ST adaptations can be used to leverage systemic principles in an individual context (e.g., encouraging an individual to explore relational patterns and multi-perspective taking). Our digital modules similarly focus on these relational perspectives and interactions, even though each participant completes the program individually. Our study focuses on the feasibility and exploratory efficacy of such an approach, rather than making conclusive claims about its effectiveness.

There is, to our knowledge, only one published study on an OSI explicitly incorporating methods and techniques associated with ST [1]. There is thus a substantial gap in the current literature. In addition, platforms such as 7 Cups, whose peer support programme has received some attention, warrant further scrutiny. For example, attrition related to the OSIs offered by platforms such as 7 Cups (https://www.7Cups.com) is a newly emerging field of research [34] to which our study could make a timely and meaningful contribution. The integration of paraprofessionals (called listeners on the 7 Cups platform), as service providers promises to provide a potential solution to the aforementioned issue of attrition and lack of engagement while retaining the scalability of OSIs. Torous and colleagues [35] identified the addition of human support and human feedback as two potential key factors reducing dropout and increasing engagement, which however warrants further study. Additionally, a recent meta-analysis indicated that paraprofessional guidance for OSIs improved effectiveness outcomes compared to unguided OSIs and was not significantly different from professional guidance [36]. While the integration of human support and human feedback might negatively impact the scalability of OSIs [35, 37], this impact might be less substantial for paraprofessional service providers such as listeners on 7 Cups, as opposed to trained mental health professionals [36]. Training paraprofessional service providers is studied in a variety of contexts and settings such as universities [37], underserved populations [38], or low- and middle-income countries [39]. While it is acknowledged as an important part of improving access to mental health care globally [40], there are to our knowledge no studies examining training paraprofessionals in ST techniques on a widely accessible online platform such as 7 Cups. We refer to “paraprofessionals” (or “listeners”) as volunteer lay people who have completed a basic training in active listening offered by 7 Cups. Although they do not function under ongoing, real-time supervision by licensed mental health professionals, 7 Cups maintains internal oversight, guidelines and training, channels to escalate services offered from lay people to professionals, and escalation procedures for safeguarding, ensuring that critical situations are referred to appropriate services. Listeners and professionals can be accessed through the same platform and can be considered to work alongside each other.
